### Concealment mechanism {16b}

The random assignment form is usually triplicated. Copies can be enclosed in an opaque envelope, with one copy provided to the patient, one copy to the researcher and one copy to the evaluator. The patient and researchers unseal it before surgery. The allocation scheme is not disclosed to the evaluators collecting outcome data throughout the study. The statistical analysts will also not know whether participants are in the STR or SCR group until the statistical analysis is completed.

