### Trial design {8}

The trial is designed as a 1:1 randomized, controlled, observers and patients double-blinded single-centre trial with two parallel groups, which will compare the STR versus SCR using autogenous fascia latas for the repair of IPMRCT. The enrolled patients were randomized in a 1:1 ratio into two treatment groups (STR group and SCR group) by a simple computer-generated randomization system (https://castoredc.com). Double-blinding was used, in which patients and evaluators were blinded to minimize ascertainment bias. It was registered in the Chinese Clinical Trial Registry (ChiCTR.org ID: ChiCTR2300073716). The study protocol was approved by our institutional review board, and all subjects will be asked to finish a written informed consent. The flow chart of the inclusion and exclusion of trial participants is given in Fig. 1.

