#### STR group

The width of the autogenous fascia latas patch was measured from the anterior to the posterior edge of the rotator cuff tendon lesion. The length of the autogenous fascia latas patch was based on the distance from the lateral edge of the rotator cuff footprint and the distance from the most medial spine of the scapula. The thickness of the autogenous fascia latas was depended on the autogenous fascia latas, however, making sure this graft was 3 to 4 mm in thickness at least. If it is less 3 mm, longer autogenous fascia latas will be harvested and folded. Two absorbable anchors with a diameter of 4.5 mm (GRYPHON for the medial row and VERSALOK for the lateral row; DePuy Mitek Synthes, Raynham, MA) were placed on the medial line of the footprint. The anchors were sutured through the lateral autogenous fascia latas patch, which was 2 cm away from the lateral end, and the traction wire was sutured at the medial end of the autogenous fascia latas patch. The guide pin passed through the subacromial from the lateral portal, ran along the supraspinatus muscle to the most medial part of the spine of the scapula, and penetrated the dorsal skin. The traction wire was pulled medially to pull out the autogenous fascia latas patch under the acromion, and then the wire of the anchor was knotted to fix the autogenous fascia latas graft in a double-row style. A transverse incision of approximately 3 cm in length was made at the most medial side of the scapular spine to expose the medial end of the patch and the spine of the scapula. An absorbable lupine anchor with a diameter of 5.5 mm (Lupine, Depuy Synthes) was implanted at the most medial side of the scapular spine, and the autogenous fascia latas graft was sutured and fixed under the appropriate tension. The incision was sutured layer by layer, and the operation was completed.

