## Assignment of interventions: blinding

### Who will be blinded {17a}

In this study, double blinding was used, in which surgeons were aware of the surgical protocol. Evaluators and patients were blinded, to minimize ascertainment bias.

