### Procedure for unblinding if needed {17b}

Because a surgical procedure is involved, the surgeons including the principal investigator were unblinded to the trial, and the evaluators collecting outcome data did not join the operation and were blinded throughout the study. When there is serious adverse event reporting and harms or the trial is finished, it will be unblinded.

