#### Quality control

To improve test reliability and reduce differences between operators, the following measures should be taken:Outpatient department by Chief Physician [name];Operations were led by [name].Photos and video recordings were taken for each operation.One person is responsible for the evaluation and statistical analysis of the test data.

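### The patient opens the allocation form before surgery, so the patient blinding claimed elsewhere in the protocol cannot hold as written

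*Protocol article*

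**What the plan says.** Concealment mechanism {16b} describes a random assignment form in three copies that can be placed in an opaque envelope, "with one copy provided to the patient, one copy to the researcher and one copy to the evaluator". The next statement is "The patient and researchers unseal it before surgery". The same section then says: "The allocation scheme is not disclosed to the evaluators collecting outcome data throughout the study". It adds that the statistical analysts do not know the arms until the analysis is complete.

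The blinding claims are these:
- Abstract, Methods: observers and patients are blinded.
- Trial design {8}: "Double-blinding was used, in which patients and evaluators were blinded to minimize ascertainment bias".
- Who will be blinded {17a}: "Evaluators and patients were blinded, to minimize ascertainment bias".
- Procedure for unblinding {17b}: evaluators take no part in the operation and stay blinded throughout. On lifting the blind it says: "When there is serious adverse event reporting and harms or the trial is finished, it will be unblinded".

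Quality control states: "One person is responsible for the evaluation and statistical analysis of the test data". The section on the steering committee {5d} likewise gives evaluation and counting of the data to one person.

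**The concern.** The concealment procedure undoes the blinding that the design relies on. Once the patient has read the form, nothing later in the protocol can restore patient blinding.

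The outcomes are sensitive to this. The primary outcomes are the ASES and Constant-Murley scores. VAS pain is secondary. The retention section {18b} refers to questionnaires completed at follow-up visits, and the data collection section says that the function scores also cover patient satisfaction. Any part that the patient reports can be moved by knowing which operation was done.

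The likely direction is also clear. The Objectives hypothesise that STR is better, and the Discussion calls it theoretically superior. A difference in favour of STR could then mix a surgical effect with an expectation effect, and the trial could not properly be reported as double-blind.

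**Working it through.** **Step 1: the patient.**
- {16b}: the patient gets a copy, and the patient and researchers open the form before the operation.
- Abstract, {8} and {17a}: the patient is blinded.
- {17b}: the blind is lifted for serious adverse events or at trial end. Opening an envelope before surgery is neither.
- Postoperative scores are collected at 3, 6, 12 and 24 months, all after the form has been opened.

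No section says that the form carries only a code, or that the patient's copy stays sealed. As written, patient blinding fails for every participant.

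**Step 2: the evaluator.**
- {16b} lists the evaluator as a recipient of a copy.
- {16b} does not list the evaluator among those who open it, and says that allocation is withheld from evaluators.
- {17b} says that evaluators stay blinded throughout.

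This is an inconsistency: no purpose is given for a copy that its holder must not read. It does not show that evaluators are unblinded.

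**Step 3: the analyst.**
- Quality control and {5d} give evaluation and statistical work to one person.
- {16b} treats evaluators and blinded statistical analysts as separate groups.
- Interim analyses {21b} uses independent statisticians, and {5d} mentions a statistician consulted throughout.

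The division of roles is stated in two incompatible ways.

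**Step 4: illustration of what is at stake.** Inputs from Sample size {14}: SD 5.8, two-sided alpha 0.05, power 0.90, 25 per group, ASES means 87.6 and 93.1.

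The plan's own figure comes first. The section states no target difference; 93.1 − 87.6 = 5.5 is inferred. A two-sample t test with difference 5.5 and SD 5.8 needs n = 24.4, rounded up to 25 per group, with power 0.907 at 25. The stated 25 is reproduced.

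Now set the true effect to zero and assume that knowledge of the arm shifts ASES by b points in favour of STR. The standard error of the difference is 5.8 × √(2/25) = 1.640. The noncentrality is b / 1.640, with 48 degrees of freedom. The chance of two-sided p<0.05 is:

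| Assumed shift b | Noncentrality | Chance of p<0.05 |
|---|---|---|
| 0 | 0 | 5% |
| 1 | 0.61 | 9.2% |
| 2 | 1.22 | 22.3% |
| 3 | 1.83 | 43.3% |

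The shift b has no source in the documents. The contradiction in Step 1 does not depend on this table.

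**The case against.** The best defence is that the envelope text reads like a general description (the form is usually made in triplicate, copies can be enclosed), while the blinding claim is made three times and is plainly the intention. On that view {16b} is loose drafting. This does not remove the problem. The statement that the patient opens the form is flat and unqualified, and site staff who follow it would break the blind. The Data Availability section calls the article the full protocol, so the article points to no fuller text that might settle the matter. It is also a contradiction between statements, not an omitted detail.

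Other objections do stand, and they limit what can be said. A reader might infer the following, which the documents do not support:
- **That evaluators are unblinded.** They receive a copy but are not said to open it, and non-disclosure to them is stated.
- **That the one person in Quality control reads the images and so sees where the graft is fixed.** No section says who reads the MRI or X-rays, or that this person scores motion or Constant-Murley.
- **That the scar reveals the arm.** For STR the protocol says "A transverse incision of approximately 3 cm in length was made at the most medial side of the scapular spine", and it describes no such incision for SCR. Whether the scar can be seen at scoring depends on how patients are dressed and examined, which is not stated.
- **That the primary score is wholly patient-rated.** The documents do not say this in words, and they name two primary scores. The exposure applies to whatever parts the patient reports.
- **That the false-positive rate will be 22% or 43%.** These figures follow only from an assumed shift.

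**Conclusion.** The point holds for patient blinding and must be fixed: {16b} is wrong as written, because it contradicts the Abstract, {8}, {17a} and {17b}, and no other section rescues it. If {16b} is followed, all 58 planned participants would know their arm before the first postoperative score.

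The evaluator's copy and the single evaluator-analyst are two lesser inconsistencies that need reconciling. They are not evidence that assessor blinding has failed.

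The size of any resulting bias cannot be derived from the documents. The range of 9% to 43% rests on an assumed 1 to 3 point shift, SD 5.8 in both arms, 25 evaluable patients per arm and no true effect. It shows only that a modest shift would matter in a trial of this size.

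**What to change.** 1. Rewrite {16b} so that allocation is revealed only to the operating team, at surgery. No copy goes to the patient or the evaluator, and the form is kept out of any record that the evaluator sees.
2. If patients are in fact meant to know their arm, keep that procedure but remove the patient-blinding and double-blind claims from the Abstract, {8} and {17a}, bring {17b} into line, and describe the trial as not patient-blinded.
3. Amend Quality control and {5d} so that the statistician already in the plan, not the evaluator, runs the analysis under the analyst blinding stated in {16b}.
4. Trial status says that recruitment began on Jan 1, 2024. Record which procedure was actually used for patients already enrolled, so that the report can state their blinding status correctly.

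Optional low-cost safeguards, given the incision described only for STR: cover the operated area at scoring visits, and record the clinical scores before that patient's images are opened.

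The main cost is an amendment to the protocol wording and a changed envelope or web routine. None of these changes alters the sample size.

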### Implementation {16c}

This trial requires patients to sign informed consent forms. This study involves private disease information, vital information and so on. The experimental research team will strictly follow the principles of the Declaration of Helsinki and the International Ethical Guidelines for Biomedical Research Involving Humans jointly formulated by WHO and the Council for International Organizations of Medical Sciences to ensure that the subjects’ medical records (medical records/MRI imaging results, etc.) will be kept private. Any public reporting of the results of this study will not disclose the individual identities of the patients.Whether the subjects participate in the study depends entirely on their personal will.Subjects will be asked to withdraw from the study if:Some test results showed that the subjects were not suitable to continue to participate in the study;The subjects cannot cooperate with treatment or timely return visits;During the study period, the subjects developed some new health problems.

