### Criteria for discontinuing or modifying allocated interventions {11b}

Intraoperative examination found that the rotator cuff of the subject was “repairable” (if it was determined that the ruptured rotator cuff could be directly repaired during the operation, conventional repair of the ruptured rotator cuff, namely direct repair, would be performed).Deciding to withdraw from the trial at any time and for any reason.Loss to follow-up.

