### Plans to promote participant retention and complete follow-up {18b}

Study follow-up visits are combined with regular visits at the outpatient clinic to minimize patient burden. The primary outcome is set to be evaluated 3 months after the intervention. All questionnaires can be completed on the day of follow-up.

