### Methods in analysis to handle protocol nonadherence and any statistical methods to handle missing data {20c}

The loss to follow-up rate will be reduced by adherence to the strategies described above. The sample size is calculated to accommodate a loss to follow-up rate of 15% without affecting statistical power.

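### The withdrawal rule in Implementation {16c} asks patients to leave for poor cooperation, untimely visits or unsuitable test results, without saying that outcome collection continues after surgery

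*Protocol article*

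**What the plan says.** Implementation {16c} lists three situations in which a patient will be asked to withdraw. Two concern this point: "Some test results showed that the subjects were not suitable to continue to participate in the study" and "The subjects cannot cooperate with treatment or timely return visits". The third is "During the study period, the subjects developed some new health problems", which is left aside here.

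Criteria for discontinuing or modifying allocated interventions {11b} has a different list: a cuff found to be repairable at surgery, loss to follow-up, and the patient's own choice ("Deciding to withdraw from the trial at any time and for any reason"). The two grounds above are not in it.

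Two other sections set the opposite aim. Section {18b} is headed "Plans to promote participant retention and complete follow-up", and its main measure is: "Study follow-up visits are combined with regular visits at the outpatient clinic to minimize patient burden". Section {20c} says: "The loss to follow-up rate will be reduced by adherence to the strategies described above", and adds: "The sample size is calculated to accommodate a loss to follow-up rate of 15% without affecting statistical power".

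The adverse-event sections differ from each other. Adverse event management, under {18a}, treats events without discontinuing follow-up. Adverse event reporting and harms {22} keeps observing patients with severe events but removes them from the study.

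**The concern.** The allocated treatment is one operation. Once it is done, no study treatment remains to be stopped, and sling use and rehabilitation can continue whether or not the patient is in the trial. What ends on leaving the study is the collection of scores at 3, 6, 12 and 24 months, including both primary outcomes.

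The two grounds arise after randomisation. Poor cooperation, failure to attend on time and unfavourable tests plausibly go with pain, poor function or a failed graft, and may differ between arms. Asking such patients to leave would tilt the comparison towards patients who did well and complied. An analysis plan can decide how to treat missing scores, but it cannot recover scores that were never collected. The 15% drop-out allowance protects precision; it does nothing against selective loss, and the rule would spend part of it on losses that the protocol itself causes.

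**Working it through.** **1. Does the rule reach into follow-up?** The grounds speak of continuing to participate and of return visits. Both belong to the time after enrolment, and nothing restricts them to the time before surgery. No test, limit, time window or decision-maker is named, and nothing says that patients asked to leave are still assessed.

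**2. The plan's own sample size** (Sample size {14}: SD 5.8, two-sided 5%, power 90%, means 87.6 and 93.1).
- The target difference is not stated. Taking the gap between the two means, 93.1 − 87.6 = 5.5, a two-sample t test has 89.5% power with 24 per group and 90.7% with 25. The stated 25 per group is reproduced.
- 25 × 1.15 = 28.75, rounded up to the stated 29. The allowance is therefore 29 − 25 = 4 patients per arm.

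**3. Precision** (normal approximation, difference 5.5, SD 5.8; the loss rates are scenarios).
- 15% lost: 29 × 0.85 = 24.65 per group, power 91.5%.
- 30% lost: 29 × 0.70 = 20.3 per group, power 85.6%.

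**4. Bias, as an assumed illustration.** Suppose there is no true difference, 4 of 29 patients leave one arm and none leave the other. Let g be how far the leavers' mean lies below the mean of those retained. The retained mean then exceeds the whole-arm mean by (4/29) × g.
- g = 5: 0.69 points, 13% of 5.5.
- g = 10: 1.38 points, 25% of 5.5.

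**5. Upper limit.** With normal scores and SD 5.8, the worst case is that exactly the lowest 4/29 = 13.8% leave. The cut lies at z = −1.090, where the normal density is 0.2203. The shift is 5.8 × 0.2203 / (25/29) = 1.48 points, so the largest possible g is 1.48 / (4/29) = 10.7. The 10-point case is thus already close to perfect selection of the worst patients.

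**6. False-positive rate** (nominal 5%). The standard error is 5.8 × √(1/25 + 1/29) = 1.58, with 52 degrees of freedom. The noncentral t distribution gives 7.1% for g = 5 and 13.7% for g = 10.

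This formula uses SD 5.8 in both groups, although the arm that keeps its poor scorers is more spread out. If 5.8 is the SD within each subgroup, that arm's SD is √(5.8² + (4/29)(25/29)g²) = 6.05 or 6.75, and simulation (200,000 trials, exactly four poor scorers kept) gives 6.5% and 10.1%. If 5.8 is the total SD, it gives 6.6% and 12.1%. With the other SD in the sample size section, 8.1, the formula gives 6.1% and 9.4%.

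**7. Less lopsided losses.** With 3 leavers in one arm, 1 in the other and g = 5, the bias is (3/29 − 1/29) × 5 = 0.34 points. With equal numbers and equal g it is zero, but the data are still lost.

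**The case against.** The strongest reply is that the list sits among consent and privacy wording, reads like generic consent text, and only asks patients to withdraw, just after stating that taking part is voluntary. An analysis plan that is not shown may also keep these patients in the analysis. Part of this stands: how often the rule would be used is unknown. It does not remove the point. The Data Availability section calls the article the full protocol, the rule is an affirmative instruction, and analysis cannot replace uncollected scores.

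Several stronger readings are tempting, and the documents do not support them:
- A reader might infer that one late visit triggers withdrawal. The wording is about being unable to cooperate with timely visits, which can mean inability to attend at all.
- A reader might infer that a poor trial result, such as a failed graft on MRI, ends follow-up. The article does not say which tests count. It records retear among the adverse events, and Adverse event management keeps following patients with adverse events.
- A reader might infer that surgeons who know the arm choose who leaves. Surgeons are indeed unblinded {17b}, but {16c} does not say who makes the request, and the evaluators are blinded.
- A reader might infer that the plan promises to prevent informative missing data. It says only that it will promote retention and reduce loss.
- A reader might assume a 15-point deficit, giving a bias of 2.07 points and a false-positive rate of 25%. With normal scores and SD 5.8 that deficit is out of reach (step 5).

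**Conclusion.** The point holds as a defect in a stated conduct rule. Implementation {16c} can end outcome collection after surgery on two loosely worded grounds that may depend on outcome and arm, and this conflicts with the aims of {18b} and {20c}.

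The documents do not give the size of the effect. The range of 0.7 to 1.4 ASES points (ceiling about 1.5) and a false-positive rate of about 7% to 14%, somewhat lower once the unequal spread is counted, rests on three assumptions: all losses fall in one arm, they use the whole allowance of four patients, and leavers score 5 to 10 points below those retained. More even losses give less bias. The rule should be fixed, because lost scores cannot be recovered later, but nothing shows that it would by itself overturn the trial's result.

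**What to change.** Amend Implementation {16c} so that, once the allocated operation has been done, these two grounds do not end outcome follow-up:
- Record the non-adherence, the late or missed visit, or the test result, with its date and reason.
- Keep inviting the patient to every later visit, and keep late assessments with their actual date.
- Analyse the patient in the allocated arm. Outcome collection stops on these grounds only if the patient withdraws consent to follow-up.

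Leave the new-health-problems ground and all clinical management decisions as they are. Reconcile {11b}, {16c}, Adverse event management under {18a}, and {22}, so that leaving the study and ending outcome collection are kept apart throughout.

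The cost is a short amendment and a field in the case report form, with no added visits or procedures. The downside is slightly less uniform visit timing.

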## Assignment of interventions: blinding

### Who will be blinded {17a}

In this study, double blinding was used, in which surgeons were aware of the surgical protocol. Evaluators and patients were blinded, to minimize ascertainment bias.

### Procedure for unblinding if needed {17b}

Because a surgical procedure is involved, the surgeons including the principal investigator were unblinded to the trial, and the evaluators collecting outcome data did not join the operation and were blinded throughout the study. When there is serious adverse event reporting and harms or the trial is finished, it will be unblinded.

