#### Adverse event management

Adverse event recordAdverse events: various surgical complications;Serious adverse events: events that require or prolong hospitalization, cause disability, affect the patient’s working ability, endanger the patient’s life cause death, and lead to congenital malformations during the course of the clinical trial.Adverse event report

Management of adverse events: When adverse events occurred, the investigator should treat them actively and according to surgical management principles without terminating the trial or discontinuing the follow-up. For serious adverse events, in addition to active rescue, the experiment should not be terminated, and observation and follow-up should be continued. The investigator should report to the subject leader within 24 h, timely report to the ethics committee, and record the adverse event in the CRF form. All adverse events should be followed up until remission or stabilization. If the patient dies, a new patient can be enrolled.

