### Adverse event reporting and harms {22}

Management of adverse events: When mild adverse events occur, the investigator should treat them actively and according to surgical management principles without terminating the trial. For severe adverse events, in addition to active rescue, the trial should be terminated and unblind to the rescuer and participants. The observation and follow-up will be continued; however, it will be removed from the study. The investigator should report to the subject leader within 24 h, timely report to the ethics committee, and record the adverse event in the CRF form. All adverse events should be followed up until remission or stabilization. If the patient dies, the patient should be removed from the list of study participants.

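### Three sections give conflicting rules for a serious adverse event, so it is undefined who is unblinded, what stops, and whether the patient stays in the comparison

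*Protocol article*

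**What the plan says.** All places are in the protocol article.

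- **Who will be blinded {17a}:** "Evaluators and patients were blinded, to minimize ascertainment bias".
- **Procedure for unblinding if needed {17b}:** surgeons know the allocation, and evaluators are described as blinded for the whole study. The next sentence reads: "When there is serious adverse event reporting and harms or the trial is finished, it will be unblinded".
- **Adverse event reporting and harms {22}:** "For severe adverse events, in addition to active rescue, the trial should be terminated and unblind to the rescuer and participants". It goes on: "The observation and follow-up will be continued; however, it will be removed from the study".
- **Adverse event management** (under data collection {18a}): "For serious adverse events, in addition to active rescue, the experiment should not be terminated, and observation and follow-up should be continued". It says nothing about unblinding. Its definition of the trigger is broad: "Serious adverse events: events that require or prolong hospitalization, cause disability", among other outcomes.
- **Concealment mechanism {16b}:** the allocation is withheld from outcome evaluators for the whole study, and from the statistical analysts until their analysis is complete.

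**The concern.** After a serious event, the site needs one answer to each of three questions: who learns the allocation, whether anything is terminated, and whether the patient's later scores count. The protocol gives more than one answer to each. The trigger is not rare by construction, since a single readmission meets the definition.

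Two things are at stake. The first is blinding. Section {17b} covers a serious event and the end of the trial in one clause with one pronoun, and it does not exclude evaluators or analysts. Under Quality control, one person is responsible for both evaluation and statistical analysis, so a disclosure to that person would reach both functions. The second is the composition of the primary comparison. The same patient is removed under one section and followed without removal under another.

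**Working it through.** There is no stated figure to reproduce. The check sets the sections side by side.

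| Question | {17b} | {22} | Adverse event management |
|---|---|---|---|
| Term for the trigger | serious | severe | serious |
| Unblinding | yes | yes | not mentioned |
| Recipients | not named | the rescuer and participants | none |
| One patient or the trial | not stated | unclear | not applicable to unblinding |
| Termination | not mentioned | yes | no |
| Patient stays in the study | not mentioned | no, though follow-up continues | follow-up continues, no removal |

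**Step 1: can all three be followed?** No. {22} and Adverse event management disagree directly on termination, and only {22} removes the case.

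**Step 2: does {22} settle the scope left open in {17b}?** Only in part. It names recipients, and these do not include evaluators. But it speaks of terminating the trial and uses a plural for those told, while its last sentence, on death, concerns a single patient. Whether one case or the whole trial is meant stays open.

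**Step 3: what results from each way of applying the text?**

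- {22} alone: disclosure to the rescuer and participants, and the case leaves the study.
- Adverse event management alone: no disclosure, and the patient continues.
- {17b} for unblinding together with Adverse event management for follow-up: disclosure to unnamed recipients, and the patient continues to be scored.

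The three differ both in who is blinded and in whose data are analysed. Only the third combines disclosure with retained scores.

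**Step 4: scale.** The documents give no serious event rate, so the rates here are assumptions. Expected patients affected = 58 × rate:

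- 1%: 58 × 0.01 = 0.58
- 2%: 58 × 0.02 = 1.16
- 5%: 58 × 0.05 = 2.9
- 10%: 58 × 0.10 = 5.8

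For comparison, the sample size section needs 25 per group and recruits 58, which leaves 58 − 2 × 25 = 8 patients for all losses. If cases are removed, they draw on that margin; if they are kept, they do not.

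**The case against.** **{22} supplies the detail that {17b} lacks.** It names the rescuer and participants, and its context (rescue, removal of a case, continued follow-up) points to the individual patient. This stands as the more natural reading. It does not remove the contradiction with Adverse event management on termination and removal.

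**Severe and serious may be meant as different categories.** Then {22} and Adverse event management would govern different events. But the article defines only serious events, {22} sets severe against mild with nothing between, and an event that endangers life could fall under both. The conflict remains at least for those events.

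**A reader might infer that evaluator blinding is broken.** The documents do not support this. No section tells evaluators the allocation, and {16b} and {17b} both keep them blinded throughout. The fault is that the unblinding sentence in {17b} does not repeat that exclusion.

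**A reader might infer detection bias in the ASES and Constant comparison.** If {22} is applied, the affected patients' later scores leave the comparison, so biased scoring of them cannot enter it. If Adverse event management alone is applied, nobody is unblinded. The risk arises only when {17b} is combined with continued follow-up. Nor do the documents say that serious events concentrate in failed reconstructions; the safety indicators also list infection, fat embolism and deep vein thrombosis.

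**A reader might infer that the first event unblinds the whole trial.** This takes the least natural meaning of the pronoun in {17b}, and any probability attached to it would rest on assumed rates. It is not evidence of a defect.

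**Patient blinding is promised less firmly than evaluator blinding.** This is correct: the documents say throughout only for evaluators. Section {16b} also has the patient open the assignment before surgery, which is a separate problem and arises before any adverse event.

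**Conclusion.** The point holds as an internal contradiction that should be corrected. Sections {17b}, {22} and Adverse event management cannot all be followed after a serious event, and the choice between them changes who knows the allocation and whose data enter the primary comparison. The likely size is a handful of patients at most, about 0.6 to 5.8 of 58, on assumed rates of 1% to 10% and on the reading that only the affected patient is concerned. It is not shown that evaluators would be unblinded or that the primary result would be biased. Disclosing one patient's allocation for the care of a serious event is not in itself a design error.

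**What to change.** 1. Reconcile {17b}, {22} and Adverse event management on whether a serious event leads to unblinding, termination or removal, and whether this concerns the single patient or the whole trial. The care decision belongs to the sponsor and investigators. Use one defined term in place of serious and severe, or define both.
2. In {17b}, state that any unblinding during the trial discloses only the affected patient's allocation, and name the recipients.
3. In {17b}, restate the protection already in {16b}: outcome evaluators stay masked throughout, and statistical analysts until the statistical analysis is completed. An earlier point for analysts, such as database lock, would weaken what is already promised.
4. Log each unblinding with its date and recipient.

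The cost is protocol wording, submitted as an amendment, and a simple log. The operating surgeons already know the allocation, so keeping evaluators and analysts masked withholds nothing from them.
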